#### Statistical Analysis Plan

Descriptive statistics will be used to summarize dentist- and patient-level characteristics, as well as primary and secondary outcomes. Continuous variables will be reported as means and standard deviations or medians and interquartile ranges, and categorical variables will be summarized using frequencies and percentages. Results will be presented for the overall cohort and stratified by titration approach. The primary analysis will evaluate differences in mean MDA between standard and enhanced titration approaches using generalized estimating equation mixed-effects models to account for clustering of patients within dentists. The titration approach will be modeled as a dichotomous independent variable. The distribution of MDA will be assessed, and transformations will be applied if necessary to meet model assumptions.

Potential confounders at the dentist and patient level will be similarly assessed, specifically, whether they are associated with the outcome, change in MDA, and with the primary independent variable, titration approach (signs and symptoms or multimethod positioning). The primary suspected and potential confounders at the dentist level will be age, practice type, and setting, and specialty. At the patient level, demographics will be similarly assessed. Typically, suspected or potential confounders would be entered in the model, and if they retained a set level of statistical significance or changed the magnitude of association between titration method and change in MDA, they would be retained as confounders. However, in this feasibility study, it is likely that the model will not converge, especially for dentist characteristics. The inability to adjust for them will be a limitation of the study and a point of discussion. Baseline OSA severity will be adjusted as a continuous variable, and depending on the distribution, may be categorized as mild, moderate, or severe. Missing data are an aspect of feasibility that will be measured and reported as such, especially for the primary variables.

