**Methods:**

This prospective, multisite, observational feasibility study will enroll approximately 60 adult patients with physician-diagnosed obstructive sleep apnea receiving OAT from 10 dental practitioners within the South Texas Oral Health Network, with each practitioner enrolling up to 6 patients. Practitioners will apply either standard signs-and-symptoms–based titration or enhanced multimethod positioning titration, as per their usual clinical practice. Clinical, dental, and titration characteristics will be collected at baseline and follow-up visits over an approximately 8-week titration period. The primary outcome is mean disease alleviation, calculated as the product of physiologic efficacy (change in apnea–hypopnea index derived from multinight home sleep apnea testing) and objective adherence (hours of nightly oral appliance use captured via an embedded compliance tracker). Secondary outcomes include daytime sleepiness, sleep-related quality of life, patient satisfaction, oral appliance–related side effects, and bruxism. Descriptive analyses and generalized estimating equation models will be used to account for clustering of patients within practitioners.

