**Figure 1. F1:**
[figure not shown]
American Academy of Dental Sleep Medicine (AADSM) recommended framework for methods for positioning oral appliance. HRPO: high resolution pulse oximetry; HSAT: home sleep apnea test; PO: pulse oximetry; PSG: polysomnogram.

A total of 60 patients (approximately 6 per dentist) will be enrolled across 10 participating dentists over a 24-month study period, with a planned allocation favoring the enhanced titration approach to support feasibility assessment. Oral appliance therapy is delivered using MADs within routine care, with clinicians retaining discretion over device selection and design features. No protocol-driven training or mandated switching between approaches is imposed, and clinicians continue to follow their usual clinical practices. While this design enhances ecological validity, it may introduce variability related to practitioner and patient factors. These will be addressed analytically through adjustment for measured confounders and the use of generalized estimating equation models to account for clustering of patients within dentists. As a feasibility study, the primary focus is on recruitment, retention, data completeness, protocol adherence, and estimation of preliminary effect sizes to inform future interventional trials. This study protocol is reported using a structured format aligned with STROBE (Strengthening the Reporting of Observational Studies in Epidemiology) guidelines for observational studies [26].

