#### Sample Size

Sixty patients will be enrolled across 10 dentist clusters (approximately 6 patients per dentist). This sample size was determined to support feasibility objectives and to estimate variability in the primary outcome (MDA) [7,10] while accounting for clustering of patients within dentists. Assuming a 2-sided α of .05 and 80% power, the study is capable of detecting standardized differences in MDA ranging from approximately 0.82 to 0.97, depending on assumptions regarding intracluster correlation coefficients (5%‐10%) and allocation ratios between titration approaches (4:6 or 3:7). These calculations account for an anticipated attrition rate of 10%‐20%.

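### The primary model is named as two different methods at once, and if it is fitted as standard GEE on 10 dentists, its nominal 5% test rejects a true null about 10–17% of the time

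*Protocol article*

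**What the plan says.** The article describes the primary analysis in three places.

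- **Statistical Analysis Plan:** "The primary analysis will evaluate differences in mean MDA between standard and enhanced titration approaches using generalized estimating equation mixed-effects models". The same paragraph adds that "transformations will be applied if necessary to meet model assumptions".
- **Abstract, Methods:** "Descriptive analyses and generalized estimating equation models will be used to account for clustering of patients within practitioners".
- **Study Design and Setting (text after Figure 1):** confounding and clustering are to be handled partly by "the use of generalized estimating equation models to account for clustering of patients within dentists".

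The Sample Size section sets the scale: "Sixty patients will be enrolled across 10 dentist clusters (approximately 6 patients per dentist"). It continues "Assuming a 2-sided α of .05 and 80% power", and concludes that "the study is capable of detecting standardized differences in MDA ranging from approximately 0.82 to 0.97". The range reflects intracluster correlations (ICC) of 5–10% and ratios of 4:6 or 3:7 between the approaches. The article gives no working correlation, variance estimator, small-sample correction or reference distribution.

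**The concern.** GEE estimates a population-average difference and takes its standard error from a sandwich formula, which is reliable when there are many clusters. A mixed model gives each dentist a random intercept and takes its standard error from the fitted variance components. In a study this small the two can give different standard errors, intervals and p-values. As worded, two analysts could each fit a different model and both claim to follow the plan.

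The choice matters because there are only 10 clusters. If the GEE reading is followed with common software defaults, the interval for the effect of titration approach will be too narrow. A chance difference between dentists could then be read as an effect of approach. The article intends its preliminary effect sizes to inform later trials, so the false precision would carry forward.

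The transformation clause adds a smaller problem. The stated target is a difference in mean MDA, and a transformation chosen after seeing the data would change the scale of that estimate.

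**Working it through.** **1. Inputs.** From Sample Size: 10 dentists, about 6 patients each, two-sided 5% test, 80% power, ICC 0.05–0.10, ratio 4:6 or 3:7, attrition 10–20%. From Statistical Analysis Plan: baseline severity as a covariate. From Study Design and Setting: dentists who use both approaches change after three patients, while the others keep one approach.

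**2. The plan's own figure.** The formula is d = (1.960 + 0.842) × √(1/n₁ + 1/n₂), with effective size 60 / [1 + (6 − 1) × ICC].

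- ICC 0.05, 4:6: 60/1.25 = 48, split 19.2 and 28.8. d = 2.802 × 0.2946 = 0.825.
- ICC 0.10, 3:7: 60/1.50 = 40, split 12 and 28. d = 2.802 × 0.3450 = 0.967.

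This matches 0.82–0.97 with all 60 patients analysed, so the inputs are read correctly. It does not show which reference distribution the analysis will use.

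**3. Why the standard sandwich is too small.** Take equal cluster sizes and approach fixed by dentist, with J₁ and J₂ dentists per approach. The GEE estimate is then the difference between averages of dentist means. The sandwich divides each sum of squares by J² rather than J(J − 1). The ratio of its expected variance to the true variance is

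[(J₁ − 1)/J₁² + (J₂ − 1)/J₂²] / (1/J₁ + 1/J₂).

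- 4 and 6 dentists: (0.1875 + 0.1389)/0.4167 = 0.783. Standard error ratio √0.783 = 0.885.
- 3 and 7 dentists: (0.2222 + 0.1224)/0.4762 = 0.724. Standard error ratio √0.724 = 0.851.

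The ratio does not depend on ICC. The normal quantile of 1.960 in place of t on 8 df (2.306) shortens the interval again.

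**4. Simulated rejection rate under no effect.** Linear GEE, 10 clusters of 6, ICC 0.05–0.10, attrition 0–20%. Most settings used 3,000–4,000 runs (Monte Carlo error about 0.6 points).

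| How approach varies | Standard sandwich, normal reference |
|---|---|
| 4 v 6 dentists, no covariate | 11.5–13.5% |
| 4 v 6 dentists, one patient-level covariate | 12.6–14.6% |
| 3 v 7 dentists, no covariate | 15–17% |
| 3 v 7 dentists, one patient-level covariate | 15.4–17.9% |
| Some dentists use both (3–5 of 10) | about 12–15% |
| All 10 use both | about 10–11% |

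A cross-check with a standard library GEE routine at ICC 0.10 (700 runs per setting, error about 1.2 points) gave 10–13%.

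**5. After correction, approach fixed by dentist.**

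- Mancl-DeRouen sandwich with t on 8 df: 3.1–5.5%.
- The same sandwich with a normal reference: 5.4–8.3%.
- Uncorrected sandwich with t on 8 df: 7.2–12.0% without covariates.
- t-test on dentist means, 8 df: 3.9–5.5%.

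Both parts of the correction are therefore needed. The mixed-model simulation often failed to converge, and no figure from it is used.

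**The case against.** **A condensed article may leave the variance estimator to a full analysis plan.** This stands. The absence of a correction is not itself an error, and the inflated rate cannot be stated as a property of this study. What remains is the contradictory model name in the text itself, together with the fact that the named method in its standard form is unsuitable for 10 clusters.

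**The Abstract and the design section both say GEE, so the intention is clear.** Largely so, which makes the naming easy to repair. But the section that defines the primary analysis is the one that adds the second method.

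**The ratios 4:6 and 3:7 are between approaches, not counts of dentists.** This stands. A reader might infer that three or four dentists form the smaller group. The documents do not say so, and the switching described in Study Design and Setting means some dentists may contribute to both groups. The same section also says that switching is not mandated, and the eligibility text asks for one approach throughout. Those statements must be reconciled. The rate exceeds 5% under each reading, but its size depends on which applies.

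**The transformation clause is conditional and names no function.** This stands in part. A reader might infer that the clause is unworkable because MDA is zero or negative when the apnea–hypopnea index does not fall. That rules out a plain logarithm but not every transformation. The remaining issue is only which scale carries the primary estimate.

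**This is a feasibility study.** This lowers the consequence. However, preliminary comparative effectiveness is part of the primary objective, and the sample size is justified by a two-sided 5% test.

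**Conclusion.** The primary model is not uniquely fixed, because the defining sentence joins two methods and two other sections name only one. If it is read as GEE with an uncorrected sandwich and a normal reference, the nominal 5% test runs at about 10–17%, so a nominal 95% interval covers about 83–90% of the time. This assumes about 6 patients per dentist, ICC 0.05–0.10 and normally distributed outcomes.

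Two stronger statements are not supported. The first is that the planned analysis has this error rate as a fact; the article neither specifies nor excludes a correction. The second is that the rate reaches 19% or more for the planned model. Rates of 18–21% at 3 v 7 dentists arose with an added dentist-level covariate, an adjustment the plan itself expects may not be possible.

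The point should be fixed before analysis. It is not a fatal defect.

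**What to change.** Replace the hybrid name in the Statistical Analysis Plan with one of the following, and use the same name throughout:

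1. GEE with exchangeable working correlation, a bias-corrected sandwich such as Mancl-DeRouen, and a t reference on about 8 df (10 dentists minus 2 parameters).
2. A linear mixed model with a random dentist intercept and Kenward-Roger degrees of freedom.

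State that the primary estimate and confidence interval are a difference in mean MDA on the untransformed scale, with any transformed analysis as sensitivity only.

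A bootstrap that resamples dentists, or a permutation of approach labels between dentists, should not be the safeguard. A percentile bootstrap of dentists rejected a true null 17% of the time at 3:7 and 14% at 4:6 (ICC 0.05, 5 patients per dentist, 3,000 runs). Label permutation does not fit dentists who contribute to both approaches.

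The cost is a sentence or two, one software option and wider intervals. In the equal-size case with approach fixed by dentist, option 1 has expected variance proportional to 1/(J₁ − 1) + 1/(J₂ − 1). Relative to the uncorrected interval, the widening at 4:6 is √(0.533/0.326) × 2.306/1.960 ≈ 1.50. At 3:7 it is √(0.667/0.345) × 2.306/1.960 ≈ 1.64. A t interval on dentist means would widen by about 1.33 (2.306/1.960 ÷ 0.885) and 1.38 (÷ 0.851). The added width reflects what 10 dentists can support.

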## Methods

### Study Design and Setting

This is a prospective, multisite, observational feasibility study to evaluate real-world titration strategies for OAT in OSA. The study examines two titration approaches defined by the American Academy of Dental Sleep Medicine (AADSM) (Figure 1): (1) standard signs-and-symptoms–based titration and (2) enhanced multimethod positioning, which incorporates objective physiologic measures such as pulse oximetry or HSAT. Both approaches are implemented as part of routine clinical care. This study is a nonrandomized, observational investigation designed to evaluate differences in treatment effectiveness between standard signs-and-symptoms–based titration and enhanced multimethod positioning approaches. A clustered design is used, with patients nested within dentists, reflecting real-world clinical practice. Participating dentists who use both titration approaches will apply their usual method for the first 3 enrolled patients and will subsequently be asked to use the alternate approach for the remaining patients, allowing for within-practitioner comparisons. Dentists who routinely use only one titration method will continue to apply that approach consistently across all enrolled patients. For each patient, the selected titration approach is maintained throughout the titration period.

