Strengths of this study include its PBRN design, integration of objective physiologic and adherence data, and evaluation of titration strategies within routine clinical workflows. The PBRN design is a major strength of this study. PBRNs provide a validated infrastructure for evaluating clinical care in real-world settings across diverse populations and practice models [19-21]. Conducted within the STOHN and in collaboration with the National Dental PBRN, PAOSA reflects the heterogeneity of real-world dental practice and enhances the external validity and applicability of study findings [25].

Several limitations should be considered. The observational, nonrandomized design introduces the potential for residual confounding and selection bias, although the structured within-practitioner approach was implemented to reduce between-practitioner variability. The relatively short follow-up period focuses on early treatment response and may not capture long-term adherence patterns or dental changes. In addition, eligibility requirements related to language and device use may limit participation among some populations. These limitations are appropriate for a feasibility-focused study and are expected to inform the design of subsequent interventional trials. As a feasibility protocol, PAOSA is designed to generate critical data on recruitment, retention, data completeness, protocol adherence, and preliminary effect-size estimates to support future randomized or pragmatic trials. The study will also identify practical barriers and facilitators to integrating HSAT and objective adherence monitoring into routine dental workflows, both of which are essential for scalability and sustainability.

Future directions include the development of randomized or hybrid effectiveness-implementation trials to more definitively evaluate titration strategies, as well as expansion to broader populations and longer follow-up periods. Study findings will be disseminated through peer-reviewed publications, presentations at scientific meetings, and communication within the dental practice–based research network to support translation into clinical practice.

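### The primary model has one approach term that pools within-dentist and between-dentist differences, so the within-practitioner design protects the estimate only in part and no planned estimate isolates it

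*Protocol article*

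**What the plan says.** Study Design and Setting creates two kinds of dentist. Those who use both approaches treat their first three patients by their usual method and then "will subsequently be asked to use the alternate approach for the remaining patients, allowing for within-practitioner comparisons". For the others: "Dentists who routinely use only one titration method will continue to apply that approach consistently across all enrolled patients".

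The limitations paragraph in the Discussion (Summary) grants that residual confounding and selection bias are possible in a nonrandomized design. It then offers as mitigation that "the structured within-practitioner approach was implemented to reduce between-practitioner variability".

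The Statistical Analysis Plan section compares mean MDA between approaches with a model described as both generalized estimating equations (GEE) and mixed effects, with patients clustered in dentists. On the exposure it says: "The titration approach will be modeled as a dichotomous independent variable". It names no dentist fixed effect, no dentist-level mean of the exposure and no analysis of the switching dentists. It thinks it likely that a model with dentist characteristics will not converge, and adds: "The inability to adjust for them will be a limitation of the study and a point of discussion".

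Other statements pull against switching. Later in Study Design and Setting, no change of approach is said to be mandated. The fifth practitioner eligibility criterion asks for one defined approach for all enrolled patients. Study Population says the approach is applied consistently within each practice. The number of dentists expected to use both approaches is not given.

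**The concern.** Dentists who use only the enhanced approach may differ from those who use only signs and symptoms in specialty, sleep training or referral pattern. Comparing patients of the same switching dentist removes every stable dentist characteristic, measured or not, without fitting any of them. Comparing patients of different single-method dentists removes none.

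One patient-level term mixes the two comparisons. GEE clustering or a random intercept handles the correlation and the standard error; neither removes confounding at dentist level. A reader of the single coefficient could not tell which comparison drives it, and the two can disagree. This matters because the primary objective includes preliminary comparative effectiveness and the effect size is meant to inform later trials. The plan also accepts a limitation on dentist-level adjustment that its own design could partly overcome.

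**Working it through.** **Inputs from the article (Sample Size).** "Assuming a 2-sided α of .05 and 80% power"; "Sixty patients will be enrolled across 10 dentist clusters (approximately 6 patients per dentist"; intracluster correlation (ICC) 0.05 to 0.10; allocation 4:6 or 3:7; a detectable range given as "standardized differences in MDA ranging from approximately 0.82 to 0.97".

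**Step 1: the article's own figure.** Detectable difference = (1.960 + 0.842) × √[DEFF × (1/n₁ + 1/n₂)], with DEFF = 1 + (6 − 1) × ICC.
- ICC 0.05, 24 v 36: 2.802 × √[1.25 × (1/24 + 1/36)] = 0.825
- ICC 0.10, 18 v 42: 2.802 × √[1.50 × (1/18 + 1/42)] = 0.967

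This reproduces 0.82 to 0.97 with all 60 patients analysed. (With 10% to 20% loss the same formula gives about 0.86 to 1.04; that is a separate matter.) This DEFF applies to an exposure that is constant within dentist, so the calculation treats the comparison as wholly between dentists.

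**Step 2: how the single coefficient is weighted.** Let p be a dentist's proportion of enhanced patients and m = 6. Under exchangeable correlation and unit variance:
- within-dentist information I_W = Σ m p(1 − p) / (1 − ICC)
- between-dentist information I_B = m Σ (p − p̄)² / (1 + 5 × ICC)
- weight on the within-dentist contrast w = I_W / (I_W + I_B)

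**Step 3: illustration.** Assumptions not in the article: switching dentists treat 3 + 3; there is no true effect; enhanced-only dentists' patients do 0.5 SD better than standard-only dentists' patients for other reasons; switching dentists lie midway. The between-dentist contrast then estimates 0.5, the within-dentist contrast estimates 0, and the pooled bias is (1 − w) × 0.5.

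Example with 4 switching, 2 standard-only and 4 enhanced-only dentists at ICC 0.05:
- I_W = 6.0/0.95 = 6.316 and I_B = 8.4/1.25 = 6.720
- w = 6.316/13.036 = 0.484 and bias = 0.516 × 0.5 = 0.258
- pooled SE = 1/√13.036 = 0.277 and within-dentist SE = 1/√6.316 = 0.398

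Each cell below gives ICC 0.05 / ICC 0.10. RMSE is √(bias² + SE²).

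| Switching / standard-only / enhanced-only | w | Pooled bias (SD) | Pooled SE | Within SE | Pooled RMSE |
|---|---|---|---|---|---|
| 2/3/5 | 0.257 / 0.305 | 0.371 / 0.348 | 0.285 / 0.302 | 0.563 / 0.548 | 0.468 / 0.461 |
| 4/2/4 | 0.484 / 0.543 | 0.258 / 0.228 | 0.277 / 0.286 | 0.398 / 0.387 | 0.378 / 0.366 |
| 4/3/3 | 0.467 / 0.526 | 0.266 / 0.237 | 0.272 / 0.281 | 0.398 / 0.387 | 0.381 / 0.367 |
| 6/2/2 | 0.664 / 0.714 | 0.168 / 0.143 | 0.265 / 0.267 | 0.325 / 0.316 | 0.314 / 0.303 |
| 6/1/3 | 0.687 / 0.735 | 0.157 / 0.132 | 0.269 / 0.271 | 0.325 / 0.316 | 0.311 / 0.302 |

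**Step 4: simulation check.** An exchangeable GEE (400 runs, ICC 0.10) gave mean pooled coefficients of 0.37 with 2 switching, 3 standard-only and 5 enhanced-only dentists, 0.23 with 4/2/4 and 0.15 with 6/1/3. The within-dentist coefficient stayed between −0.02 and 0.01.

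**Limits.** If all 10 dentists split 3/3, w = 1 and the problem disappears. If none switches, w = 0 and there is no within-dentist contrast.

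**The case against.** - **The article is modest about its claim.** It says the structure was meant to reduce practitioner differences and concedes residual confounding. It calls non-convergence likely, not certain, and still plans to assess dentist-level confounders. A reader might infer that the protocol claims to have removed practitioner confounding; it does not. The pooled coefficient does gain protection as more dentists switch, as the falling bias in the table shows. This stands, and it limits the point to partial protection that is never shown separately.
- **A supplementary estimate may sit in a fuller analysis plan.** That is possible, and nothing in the article rules it out. But the article itself fixes the primary exposure term and itself credits the within-practitioner structure, and the mismatch between those two statements is on the page.
- **The illustration is adverse.** ICC 0.05 to 0.10 means a between-dentist SD of √0.05 = 0.22 to √0.10 = 0.32, so a 0.5 SD gap is 2.2 down to 1.6 dentist SDs. With known variance the biases would give rejection rates of 8% to 26% at a nominal 5%. A reader might take these as the study's false-positive rate. The documents do not support that: the gap and the number of switching dentists are assumed, and this is a feasibility study.
- **The within-dentist estimate is not more accurate overall.** Pooled RMSE (0.30 to 0.47) is below the within-dentist SE (0.32 to 0.56) in every split. A reader might conclude that the within-dentist estimate should replace the pooled one; these figures do not support that.
- **The within-dentist contrast has its own bias.** The usual method always comes first, so approach is confounded with order and familiarity. This stands and must be stated wherever the estimate is reported.

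**Conclusion.** The point holds in a limited form. The primary coefficient averages a contrast free of stable dentist differences with one that is open to them, and nothing in the stated plan separates the two. The mixing follows from the model and needs no assumed gap. In the splits examined, 26% to 74% of the weight is within-dentist. The size of any bias does depend on assumption: 0.37 down to 0.13 SD for a 0.5 SD gap, ICC 5% to 10% and 2 to 6 switching dentists, in proportion to the gap.

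This does not make the pooled analysis invalid or a poor choice of primary estimate. It means that the pooled number cannot by itself carry the Discussion's statement about practitioner differences. Whether any within-dentist contrast will exist is also unsettled while the article's statements on switching conflict.

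**What to change.** 1. Keep the pooled estimate as primary. In the Statistical Analysis Plan section, prespecify a supplementary model with two exposure terms: the dentist's proportion of enhanced patients, and the patient's approach minus that proportion. Report the second coefficient and its interval beside the pooled estimate.
2. State that the pooled estimate remains open to dentist-level confounding, and that the within-dentist estimate is less precise and confounded with order.
3. Reconcile the switching arrangement in Study Design and Setting with the statement in the same section that no switching is mandated, with the practitioner eligibility criterion, and with Study Population. Which arrangement applies is for the investigators to settle.
4. Report how many dentists used both approaches. If none did, remove the Discussion's statement about the within-practitioner structure.

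The cost is one derived covariate, one extra reported row and some text, with no new data or patients. The interval will be wide: about ±1.96 × 0.39 to 0.40 SD with four switching dentists. Analysis is planned for 2027, so this can still be fixed in advance.

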Sleep-related quality of life	FOSQ-10^h^ score	Secondary outcome	FOSQ-10 questionnaire	Visit 1b; Visit 2; Visit 3
Patient satisfaction	Satisfaction with dental sleep care	Secondary outcome	PSQ-18^i^	Visit 3
Patient-reported side effects	Jaw pain, tooth discomfort, bite changes	Secondary outcome	Sleep and Side effects questionnaire	Visit 1b; Visit 2; Visit 3
Physiologic sleep measures	AHI^j^, RDI^k^, SpO2 nadir, time <90% oxygen saturation	Primary outcome Component	NightOwlHSAT^l^	Visit 1b; Visit 2; Visit 3
Objective adherence	Hours of nightly oral appliance use; head position	Primary outcome component	DentiTrac compliance tracker	Continuous; summarized at Visit 2 and Visit 3
Treatment effectiveness	MDA^m^	Primary outcome	Derived (AHI × adherence)	Visit 2; Visit 3
Patient experience	Perceived benefit, willingness to continue therapy	Exploratory outcome	Patient questionnaire	Visit 3

a Variable roles: predictor variables represent dentist, patient, or clinical characteristics that may influence treatment outcomes. Outcome variables include patient-reported outcomes, clinician-observed effects, feasibility indicators, and the primary effectiveness outcome. Physiologic sleep measures and objective adherence data are combined to derive the primary outcome MDA, calculated as treatment efficacy (change in AHI measured by NightOwl HSAT) multiplied by objective adherence (hours of nightly oral appliance use recorded by the DentiTrac compliance micro tracker).

b DSM: dental sleep medicine.

c Visit definitions: Visit 1a = eligibility screening, consent, and baseline dental examination/clinical assessment; Visit 1b = oral appliance delivery and baseline questionnaires; Visit 2 and Visit 3 = follow-up visits during the titration period.

d OSA: obstructive sleep apnea.

e TMJ: temporomandibular joint disorder.

f OAT: oral appliance therapy.

g ESS: Epworth Sleepiness Scale.

h FOSQ: Functional Outcomes of Sleep Questionnaire.

i PSQ-18: Patient Satisfaction Questionnaire.

j AHI: apnea–hypopnea index.

k RDI: respiratory disturbance index.

l HSAT: home sleep apnea test.

m MDA: mean disease alleviation.

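### Transforming MDA after its distribution is seen can move the primary test away from the stated difference in means; the harm depends on the two approaches differing in shape or non-use

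*Protocol article*

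**What the plan says.** The Statistical Analysis Plan section of the protocol article fixes the target: "The primary analysis will evaluate differences in mean MDA between standard and enhanced titration approaches". The same sentence describes the method for this comparison as "using generalized estimating equation mixed-effects models to account for clustering of patients within dentists". Two sentences after that it allows a change of scale: "The distribution of MDA will be assessed, and transformations will be applied if necessary to meet model assumptions". It names no transformation, no criterion and no return to the mean scale.

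Table 1, footnote a, defines MDA as "calculated as treatment efficacy (change in AHI measured by NightOwl HSAT) multiplied by objective adherence", in hours of nightly use, with no floor. The Sample Size section expresses sensitivity on the MDA scale: "the study is capable of detecting standardized differences in MDA ranging from approximately 0.82 to 0.97". Study Design and Setting lists preliminary effect sizes for later interventional trials among the study's main products.

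**The concern.** The stated null is equal mean MDA. On a log scale the null becomes, roughly, equal geometric means. The two coincide only if the groups have distributions of the same shape. The groups are nonrandomized, and the Discussion expects that titration strategies may differ in comfort, side effects and adherence, so equal shape cannot be taken for granted.

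Footnote a also makes MDA zero for a patient who does not wear the appliance, and gives it the opposite sign for a patient whose AHI worsens. (The table row itself gives AHI times adherence; read literally, that cannot be negative but can still be zero.) A log is undefined at such values. Dropping those patients removes the non-adherent ones whom MDA was chosen to count; adding a constant gives them a weight set by the constant. At stake are the p-value for the primary comparison and the scale of the effect size handed to the next trial.

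**Working it through.** **1. The plan's own figure.** Inputs from Sample Size: N = 60, m = 6 per dentist, ICC 0.05 to 0.10, allocation 4:6 or 3:7, two-sided alpha 0.05, 80% power. With N_eff = N / (1 + (m − 1) × ICC) and d = (1.960 + 0.842) / √(N_eff × a × (1 − a)):

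- ICC 0.05, a = 0.4: N_eff = 60 / 1.25 = 48; d = 2.802 / √(48 × 0.24) = 2.802 / 3.394 = 0.825.
- ICC 0.10, a = 0.3: N_eff = 60 / 1.5 = 40; d = 2.802 / √(40 × 0.21) = 2.802 / 2.898 = 0.967.

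The range reproduces with all 60 patients analysed (whether attrition is included is a separate matter). It is a difference in mean MDA divided by the SD of MDA, so it does not carry over to a transformed outcome.

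**2. How a log changes the quantity.** The article gives no SD or distribution for MDA, so everything from here on rests on assumed inputs. For a lognormal outcome, geometric mean = mean × exp(−s²/2), where s is the SD on the log scale.

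- Equal means of 60, s = 0.5 (standard) and 0.8 (enhanced): 60 × exp(−0.125) = 52.95 and 60 × exp(−0.32) = 43.57.
- Raise the enhanced mean to 66: 66 × exp(−0.32) = 47.93, still below 52.95. The order of the groups reverses.

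Welch tests on 24 versus 36 patients, without clustering and with equal means, rejected as follows: s = 0.6 in both groups, 4.9% raw and 5.1% log; s = 0.5 versus 0.8, 5.1% and 20.2%; s = 0.4 versus 1.0 (extreme), 8.6% and 60.5%.

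**3. Zero and negative values.** Building MDA as AHI reduction times hours, the share at or below zero was 0.8% to 11.1% over six assumed settings.

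**4. Clustered simulation, equal mean MDA of about 70 in both groups.** Assumptions: each dentist uses one approach; 6 patients per dentist; ICC 0.05; baseline AHI lognormal with median 20 and log-SD 0.5; AHI reduction about 50% in the standard group (SD 0.25), calibrated in the enhanced group to equalise the means; hours of use normal with mean 6.5 and SD 1.2, and 0 for non-users; 20,000 trials; two-sided 5% t-test on dentist means. Rejection of the true null:

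| Non-users, standard vs enhanced | Raw | log(MDA+1), negatives set to 0 | log, non-positives dropped | Shifted square root |
|---|---|---|---|---|
| 5% vs 5%, 4 vs 6 dentists | 4.7% | 4.8% | 4.9% | 5.1% |
| 5% vs 20%, 4 vs 6 dentists | 4.6% | 10.8% | 11.9% | 5.6% |
| 5% vs 25%, 4 vs 6 dentists | 4.7% | 16.0% | 17.9% | 7.0% |
| 5% vs 20%, 3 vs 7 dentists | 4.3% | 7.8% | 10.8% | 5.1% |

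Repeats of the second row with separate code gave 4.7% raw, 10.5% and 12.0% for log(MDA+1), and 11.9% and 12.8% after dropping. The two log versions err in opposite directions: nearly all false positives say enhanced is worse with the constant added, and nearly all say it is better with non-positives dropped.

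Smaller imbalances, in the same column order for the two log versions: 5% vs 10%, 5.2% and 5.5%; 2% vs 5%, 4.7% and 5.0%; 10% vs 5%, 6.6% and 5.1%. At 5% vs 15% rejection was about 7%.

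**5. A true benefit.** With means of 56 and 88 and non-users 5% vs 15%, power was 34.5% raw, 10.5% with log(MDA+1) and 67.2% after dropping non-positives.

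**6. Choice of scale alone.** With identical distributions in both groups, each single scale rejected in 2.6% to 4.9% of runs, but at least one of six scales rejected in 8.4%.

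**The case against.** **Conditional wording.** The plan transforms only where model assumptions require it, and it also adjusts for baseline severity. A reader might infer that skewness makes a transformation near certain. The documents do not support that. In the same data model, pooled MDA failed a Shapiro test in 95% to 99% of trials, but residuals after linear adjustment for baseline AHI failed in only 34% to 45%. This stands.

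**Model not fully stated.** A reader might also say that the planned GEE needs no normal outcome, so the reason for transforming is empty. But the article gives neither an identity link nor a robust variance, and its phrase for the model mixes GEE with mixed effects. Under a mixed model, checking distributional assumptions is ordinary practice. The argument is sound for a GEE with identity link and robust variance, but the article does not commit to one.

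**Chosen inputs.** The plan names no log, constant or dropping of patients. The inflation needs a large gap in non-use, with more non-users under enhanced titration, whereas the Discussion anticipates better adherence there. Exact zeros also require that the appliance was never worn in the summary period, by patients who agreed to use it. All of this stands and limits the size of the point.

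**Scope.** This is a feasibility study, and outcomes will also be summarised by approach, possibly as means and SDs on the original scale. An MDA-scale effect may therefore still be recoverable, though the option of medians instead means that it is not assured.

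**Detail left to an analysis plan.** The trigger and the handling of zeros may well be set in a document not shown, and their absence is no fault here. The point rests on the rule that the article does state, which lets the scale of the primary comparison depend on the outcome data.

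**Conclusion.** The point holds in conditional form. The stated rule can replace the stated target, a difference in mean MDA, with another quantity once the outcome distribution is known. Under the assumed distributions, a log roughly doubles the false-positive rate, or more, when non-use differs strongly between approaches. It has almost no effect when non-use is similar, and a square root is mild.

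It would go too far to say that the result will change or reverse, or that the plan is biased for or against enhanced titration. The direction depends on how non-positive values are handled, and nothing in the article shows how far the groups will differ. The more certain consequence of transforming is a mismatch of scale with the detectable range and with a preliminary effect size for mean MDA. The point is worth correcting but does not undermine the study.

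**What to change.** Replace the transformation sentence in the Statistical Analysis Plan section with:

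*The primary comparison is the difference in mean MDA on its original scale (GEE, identity link), adjusted for baseline OSA severity as planned, with zero and negative values kept, whatever the observed distribution. Inference uses a cluster-robust variance with a small-sample correction and a t reference distribution suited to 10 dentists. Transformed or rank-based analyses are sensitivity analyses only.*

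The small-sample correction is essential. On untransformed MDA with equal means, an uncorrected robust-variance z-test rejected in about 12% to 13% of trials with 4 versus 6 dentists and 14% to 17% with 3 versus 7, as bad as the log analyses above. The near-5% rates for raw MDA come from a t-test on dentist means; the corrected GEE was not itself simulated, so its level should be checked before the wording is final.

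The cost is wording only, with no new data. If the groups share a skewed shape and differ only in level, some power is lost (35% raw versus 40% with a square root in the simulation), and the correction widens intervals slightly. Recruitment is projected through January 2027 with analysis to follow, so the rule can be set before the distribution is seen.
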